Our study differs from these published studies in the following ways:Our study includes only tumors ≥11 mm (microcarcinomas are not eligible), whereas all of the studies cited in Table 1, with the exception of the study by Sippel et al. [32], included a large proportion of microcarcinomas (in Ahn et al. [31] for example, 90% of the tumors were T1 with a mean tumor size of 1.1 +/− 0.6 cm);Thyroglobulin measurements will be evaluated before and after the administration of RAI to evaluate the effect of RAI ablation and eliminate this bias found in most of these studies in which outcomes were evaluated after RAI ablation in most or all patients;Finally, our study is designed with a non-inferiority margin of 5% and an alpha level set at 0.025, whereas the study by Viola et al. [34] is significant but with a non-inferiority margin of 15% and an alpha of 0.05.

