#### Secondary objectives

To compare total thyroidectomy and radioactive iodine (^131^I) to total thyroidectomy with bilateral prophylactic central compartment neck dissection and 131I in terms of:Thyroglobulin levels after surgery alone (usTg/T4) measured while on T4 treatment, 8+/−2 weeks postoperatively, before stimulation and administration of radioactive iodinePercent of patients in complete remission (excellent response) at 3 and 5 years after randomization, as defined by a normal neck ultrasound and usTg/LT4 ≤ 0.2 ng/m. The endpoint of 5 years reflects the data from a prospective multicenter study of 715 patients reporting that 81% of recurrences occurred within 5 years,[43] and from a retrospective study of 1020 patients followed for 10 years reporting that all structural recurrences occurred within 8 years, with 77% occurring within 5 years [44].Percent of patients at 1, 3, and 5 years after randomization with structural incomplete response in the neck defined by a malignant lesion in the neck detected by ultrasound and confirmed by cytology (and/or Tg in the needle washout fluid >10ng/ml). Cytology will be mandatory for suspicious lesions measuring 8mm or more in the smallest diameter; lesions with suspicious features on ultrasound but measuring <8 mm may undergo cytology at the discretion of the center’s principal investigators.Percent of patients at 1, 3, and 5 years after randomization with biological incomplete response defined by a normal neck ultrasound and absence of disease detected on other conventional or metabolic imaging (^131^I, ^18^FDG-TEP), if performed, associated with a serum Tg/LT4>0.2 ng/mlPercent of patients at 1, 3, and 5 years after randomization with an indeterminate response defined by a suspicious lesion on neck ultrasound without cytological proof of disease and/or detection of TgAbPercent of patients at 1, 3, and 5 years after randomization with diagnosis of distant metastases on metabolic imaging (^131^I, ^18^FDG-TEP) or cross-sectional imaging, and confirmed cytologically (except for metastases with ^131^I uptake) or with repeat imaging at 6 months (if cytology not possible)Percent of patients at 1, 3, and 5 years after randomization having undergone further treatment (surgery or 2nd therapeutic administration of ^131^I, number of retreatments per patient and indication for each retreatment)At 1 year: percent of patients with persistent hypoparathyroidism with supplementation and/or persistent vocal fold paralysis; subjective dysphonia (Voice Handicap Index)[45] and dysphagia (SWAL-QOL)[46] (questionnaires in their validated French versions) compared between groups after randomization: Quality of life SF36[47], EuroQol EQ-5D,[48] Anxiety (State-Trait Anxiety Inventory-STAI)[49]Cost-utility analysis.

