##### Radioactive iodine

All patients will have Tg/LT4 measured 8 +/− 2 weeks postoperatively, before stimulation with recombinant human thyrotropin (rhTSH).

Then, for all patients (whichever the group), radioactive iodine will be administered after 2 months but within 4 months postoperatively: 30 mCi (1.1 GBq) ^131^I after stimulation with human recombinant thyrotropin (rhTSH)

A ß-HCG test (serum or urine) will be performed before any radioiodine administration.

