### Outcomes: Secondary criteria

#### Oncologic secondary criteria

Thyroglobulin levels after surgery alone (ultrasentive thyroglobuliin, usTg/T4) measured while on T4 treatment, 8 +/−2 weeks postoperatively, before stimulation or administration of radioactive iodinePercent of patients in complete remission (excellent response) at 3 and 5 years after randomization, as defined by negative imaging and either unstimultaed ultrasensitive thyroglobulin while on L-thyroxine treatment (usTg/LT4) ≤ 0.2 ng/mL) without anti-Tg antibodies (TgAb) or TSH-stimulated Tg<1ng/mL

The endpoint of 5 years reflects the data from a prospective multicenter study of 715 patients [Brassard M et al J Clin Endocrinol Metab 2011] reporting that 81% of recurrences occurred within 5 years, and from a retrospective study of 1020 patients followed for 10 years [Durante C et al J Clin Endocrinol Metab 2013] reporting that all structural recurrences occurred within 8 years, with 77% occurring within 5 years.Percent of patients at 1, 3, and 5 years after randomization with structural incomplete response in the neck defined by the presence of structural or functional evidence of disease, with any Tg level, with or without anti-Tg antibodiesPercent of patients at 1, 3, and 5 years after randomization with biological incomplete response defined by negative imaging and suppressed Tg ≥1 ng/mL or stimulated Tg≥10ng/mL or rising anti-Tg antibody levelsPercent of patients at 1, 3, and 5 years after randomization with an indeterminate response defined by nonspecific findings on imaging studies and/or faint uptake in thyroid bed on RAI scanning (if performed) and/or on stimulated Tg detectable but <1ng/mL and/or stable or declining TgAb in the absence of structural or functional diseasePercent of patients at 1, 3, and 5 years after randomization with diagnosis of distant metastases on metabolic imaging (^131^I, ^18^FDG-TEP) or cross-sectional imaging, and confirmed cytologically (except for metastases with ^131^I uptake) or with repeat imaging at 6 months (if cytology not possible).Percent of patients at 1, 3, and 5 years after randomization having undergone further treatment (surgery or 2nd therapeutic administration of 131I, number of retreatments per patient and indication for each retreatment)

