### Statistical methods

#### Statistical methods for primary and secondary outcomes

Descriptive summary statistics will be provided for continuous demographic, laboratory, and clinical variables. The descriptive summary statistics will include number of patients, means and standard deviations for quantitative variables, and percentages for qualitative data.

Subject demographic and baseline characteristics will be summarized by treatment group. The Student test will be used for the continuous variables (or non-parametric test if variables are not normally distributed), and the chi-square test will be used for the categorical variables.

Primary outcomes s1

The main endpoint will be analyzed 1 year after randomization of the last patient, once all the CRF will have been collected and the database has been cleaned. The analysis will be performed when all patients will have 1 year of follow-up, and no lost of follow-up will be tolerated.

A patient will be in remission if the requirements are met at 1 year following randomization. Conversely, a patient will be considered to not be in remission if the criteria are not met at 1 year following randomization. In the absence of censored data, the proportion of patients in complete remission will be calculated as a percentage.

Since the study is designed as a non-inferiority study, the primary analysis will be carried out by considering all evaluable patients (per-protocol population), as this is the most conservative approach in this context. Patient will be considered as evaluable if the treatment and the follow-up conform to the study protocol (diagnostic tests performed) and if the patient does not have detectable anti-Tg antibodies. A sensitivity analysis using the intent-to-treat (ITT) population, considering all patients in their initial group of randomization, will also be performed, to test the robustness of the results.

The observed difference in patients in complete remission (∆) and its 95% unilateral confidence interval will be calculated. If the unilateral confidence interval does not include the −5% clinically relevant difference (∆L), then the TT alone strategy will be considered as non-inferior to the TT + PCND strategy.

All statistical analyses will be performed using the SAS® software.

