Secondary outcomes s1Unstimulated thyroglobulin levels between groups will be compared between groups using a chi-square test.The rate of patients in complete remission at 3 and 5 years will be compared between groups using a chi-square test.The rate of patients in with structural incomplete response, biological incomplete response, indeterminate response, distant metastases, or further treatments at 1, 3, and 5 years will be compared between the 2 groups using a chi-square test for each type of response.

For these secondary criteria we expect, based on retrospective series comparing the two surgical techniques (total thyroidectomy alone or total thyroidectomy + PND), rates of incomplete response or re-treatement in the range of the following:Difference in locoregional control = 6.9% at 10 years [1]Difference in rate of recurrence = 4.6% at 3 years [2]Difference in rate of retreatment = 8.2% at 5 years [3]Rate of structural recurrence = 1.4% at 8 years [44]The rate of patients at 1 year with persistent hypoparathyroidism requiring medication and/or with persistent vocal fold paralysis will be compared between groups using a chi-square test; subjective dysphonia (Voice Handicap Index) and subjective dysphagia (SWAL-QOL) toxicities will be compared using a Student test for each time of evaluation (or a Kruskall-Wallis non-parametric test if they are not normally distributed).Quality of life and anxiety: The investigator will inform the patient on the objective of QoL data collection. QoL data may be not exploitable in case of great number of missing questionnaires. Data will be analyzed according to the scoring manual of each questionnaire. A longitudinal analysis using a mixed model will be used to take into account of repeated QoL assessment and the initial value. If this analysis shows a significantly different effect between groups or an interaction between treatment and time, an analysis of the treatment effect on quality of life will be carried out at each time. Mean sub-scale scores will be compared using a Student test for each time of evaluation (or a Kruskall-Wallis non-parametric test if they are not normally distributed).

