## Discussion

The main objective of this study is to show the non-inferiority of total thyroidectomy alone as compared to a total thyroidectomy with a bilateral prophylactic central neck dissection in clinically low-risk patients. This trial will ultimately include a number of patients with intermediate risk factors (Haugen) found on finally pathology. This is the rationale for administering an ablative dose of RAI to all patients, despite the fact that RAI is no longer systematically indicated for pathologically low-risk tumors.(Leboulleux 2022). A secondary objective, however, is to also compare the thyroglobulin levels 8 weeks after surgery and before administration of RAI in each group, to evaluate outcomes without RAI. The need for a total thyroidectomy for low-risk tumors has also been questioned (Haugen); unfortunately, this clinical trial is designed only to answer one question, that is, the utility of PND, and is not suited to answer other questions concerning “downgrading” of surgery for low-risk tumors.

Centers not including patients may be subjected to closing. Centers in France and outside of France may be added as investigators, subjected to approval of an amendment to the study by the national authorities (National Agency for Drug Safety, “Agence Nationale de la Sécurité du Médicament et des Produits de Santé, ANSM) and the French nationa research ethics committee (Comité de Protection des Personnes, CPP). In the event of other amendments, they will also be subjected to the above-cited national authorities for safety and ethical evaluation. The promotor data managing committee will communicate any approved protocol modifications to the participating centers.

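### Post-surgical thyroglobulin is defined as a level but assigned a chi-square test, with no cut-off set for it; splitting the levels would lose power

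*Protocol article*

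**What the plan says.** The Secondary objectives list "Thyroglobulin levels after surgery alone (usTg/T4) measured while on T4 treatment", taken at 8 ± 2 weeks after surgery and before stimulation or RAI. The Oncologic secondary criteria repeat it as "Thyroglobulin levels after surgery alone". Neither section gives a threshold or categories for this endpoint.

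The protocol gives the endpoint a clear purpose. Background and rationale sets the trial apart from earlier studies because "Thyroglobulin measurements will be evaluated before and after the administration of RAI to evaluate the effect of RAI ablation". The Discussion says the aim is to "compare the thyroglobulin levels 8 weeks after surgery and before administration of RAI in each group, to evaluate outcomes without RAI". Every patient then receives RAI: "for all patients (whichever the group), radioactive iodine will be administered after 2 months but within 4 months postoperatively".

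Under Secondary outcomes in the Statistical methods, the planned analysis is that "thyroglobulin levels between groups will be compared between groups using a chi-square test". The same section handles other continuous variables differently. For baseline data, "The Student test will be used for the continuous variables (or non-parametric test if variables are not normally distributed", with chi-square kept for categorical data. The Voice Handicap Index and SWAL-QOL scores get a Student test or a Kruskal-Wallis test.

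**The concern.** The endpoint and the test do not fit. A chi-square test works on counts in categories, so it cannot be applied to Tg in ng/mL until someone decides where to split it. Every other outcome given a chi-square test in the secondary analyses is a rate of patients. Tg is the only level treated this way.

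The missing split cannot be read off with confidence from elsewhere. The value 0.2 ng/mL belongs to the response definitions at 1, 3 and 5 years. The Oncologic secondary criteria also use a suppressed Tg of 1 ng/mL or more for biological incomplete response. Neither is tied to the 8-week sample.

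The protocol relies on this comparison to show what surgery achieves before RAI. A test that reduces each level to above or below a line discards information from that comparison and leaves its exact content undefined.

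**Working it through.** **The plan's own figure.** The protocol gives no effect size, distribution or power for the Tg endpoint, so there is nothing to reproduce. The 299 per group comes from the primary endpoint. It follows if 95% remission is assumed in both arms (the rate is not stated): n = (1.960 + 0.842)² × 2 × 0.95 × 0.05 / 0.05² = 298.3, rounded up to 299. It is used below only as a realistic number per arm.

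**Endpoint against test.**

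| Outcome | Type | Planned test |
|---|---|---|
| Continuous baseline variables | level | Student or non-parametric |
| Voice Handicap Index, SWAL-QOL | score | Student or Kruskal-Wallis |
| Remission, other responses, metastases, retreatment | rate | chi-square |
| Tg at 8 ± 2 weeks | level | chi-square |

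Only the last row breaks the pattern.

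**Efficiency in large samples.** Take log Tg as normal with a shift between arms, and split it where a fraction p lies at or below the cut-off c. Relative to the rank-sum test, the efficiency of the split is [φ(c)² / (p(1 − p))] ÷ (3/π). At p = 0.5 this is (0.3989² / 0.25) ÷ 0.955 = 0.637 / 0.955 = 0.67. At p = 0.6, 0.7, 0.8 and 0.9 it is 0.65, 0.60, 0.51 and 0.36. This assumes all values are measurable.

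**Power with an assay floor.** Assumptions, none of them from the protocol:
- Log-normal Tg with log-SD 1.5.
- A shift of 0.35 on the log scale, which is 0.35 / 1.5 = 0.23 SD.
- 299 per arm and two-sided 5%.
- Values below the floor set to the floor.
- 3,000 simulated trials per row, and chi-square without continuity correction.

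| Floor (ng/mL) | Median (ng/mL) | At or below floor | Rank-sum | Chi-square, cut 0.2 | Chi-square, cut 1.0 |
|---|---|---|---|---|---|
| 0.1 | 0.1 | 50% | 74% | 61% | 34% |
| 0.1 | 0.2 | 32% | 77% | 63% | 47% |
| 0.1 | 0.45 | 16% | 78% | 55% | 60% |
| 0.1 | 1.0 | 6% | 80% | 41% | 64% |
| 0.2 | 0.1 | 68% | 66% | 60% | 33% |
| 0.2 | 0.2 | 50% | 73% | 62% | 48% |
| 0.2 | 0.45 | 29% | 79% | 57% | 61% |
| 0.2 | 1.0 | 14% | 79% | 42% | 64% |

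The median and the share at or below the floor refer to the lower arm. Repeat runs move an entry by one to three points, so the ranges are best read as about 66–80% for the rank-sum test and about 34–65% for chi-square.

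The smallest loss is about 5 points (floor 0.2, median 0.1, cut 0.2: 66% against 60%). The largest is about 40 (floor 0.1, median 0.1, cut 1.0: 74% against 34%).

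**When the loss is small.** A second simulation used a 0.25 SD shift and put the cut-off exactly at the assay limit. Rank-sum against chi-square was 79% against 70% with half of one arm undetectable, 72% against 66% with 70%, and 48% against 47% with 90%. Type I error was about 5% for both tests. A cut-off at the limit is not enough by itself: with floor and cut both 0.2 and a median of 1.0, only 14% are undetectable and the loss is still about 38 points.

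**The case against.** The strongest defence is that a chi-square test on categorised Tg is a sound procedure, that 0.2 ng/mL recurs throughout the protocol and is a natural reading, and that a condensed article may leave the category to the analysis plan. Much of this stands. A missing cut-off alone would not be a finding. What remains is that the article names the endpoint as levels and names a test that does not compare levels, against its own practice for other continuous variables.

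A reader might infer four stronger claims that the documents do not support:

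- **That this is the trial's only oncologic evidence on surgery.** Both arms receive the same RAI, so the randomised comparisons at 1, 3 and 5 years also inform on the surgical difference, in the presence of RAI. Stimulated Tg and neck ultrasound are also collected at the time of RAI, though they are not listed as endpoints.
- **That the test is invalid.** Once Tg is categorised, its type I error is about 5%. The trouble is the undefined category and the lost power.
- **That the cut-off will be chosen to suit the result because the trial is open.** The blinding section says the data analyst will not know the allocation. That lowers the risk, although it does not define the comparison.
- **That the power loss is a fixed figure, such as 20 points.** It depends on the median, the assay floor and the cut-off, none of which the protocol gives for this endpoint.

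It is also fair to say that how anti-Tg antibodies are handled here is detail rather than error. They are measured at the same visit, so the analysis can use them.

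**Conclusion.** The point holds as a mismatch between a stated endpoint and a stated test. The 8-week Tg comparison cannot be carried out on levels with the test named, and no cut-off is assigned that would turn it into a comparison of proportions.

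Under the log-normal assumptions above, dichotomising loses roughly 5 to 40 points of power against a rank-sum test. The lower end applies when most patients are undetectable and the cut-off sits at the assay limit. The distribution, shift, median and floor are all assumptions, so the range shows the direction and possible scale of the loss and does not predict it.

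The endpoint is secondary and carries no stated hypothesis or power. The primary non-inferiority conclusion is unaffected. The point is still worth correcting because the protocol uses this comparison to judge outcomes before RAI.

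**What to change.** In the secondary outcomes of the Statistical methods, replace the chi-square test for this endpoint with a Wilcoxon rank-sum test (Kruskal-Wallis is equivalent for two groups). Give values below the assay limit a tie at the lowest rank, and analyse patients without anti-Tg antibodies at that sample. This brings the endpoint under the rule the protocol already uses for continuous variables.

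If a proportion is also wanted, state its cut-off now, for example the protocol's own 0.2 ng/mL, and report that comparison as supportive.

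The cost is one or two sentences in the protocol or analysis plan. The follow-up schedule already includes Tg and anti-Tg antibodies at 8 ± 2 weeks, so no new data, visits or patients are needed.

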**Trial design and methods:**

Prospective randomized open multicenter phase III trial including patients with 11–40-mm papillary thyroid carcinoma (Bethesda VI) or suspicious cytology (Bethesda V) confirmed malignant on intra-operative frozen section analysis, with no suspicious lymph nodes on a specialized preoperative ultrasound examination. Patients will be randomized 1:1 into two groups: the reference group total thyroidectomy with bilateral prophylactic central neck dissection, and the comparator group total thyroidectomy alone. All patients will receive an ablative dose of 30mCi of radioactive iodine (RAI) within 4 months of surgery. The primary outcome is to compare the rate of excellent response at 1 year after surgery between the groups, as defined by an unstimulated serum thyroglobulin (Tg) level ≤ 0.2 ng/mL with no anti-Tg antibodies, an normal neck ultrasound and no ectopic uptake on the post-RAI scintiscan. Non-inferiority will be demonstrated if the rate of patients with excellent response at 1 year after randomization does not differ by more than 5%. Setting the significance level at 0.025 (one-sided) and a power of 80% requires a sample size of 598 patients (299 per group). Secondary outcomes are to compare Tg levels at 8 +/− 2 postoperative weeks, before RAI ablation, the rate of excellent response at 3 and 5 years, the rate of other responses at 1, 3, and 5 years (biochemical incomplete, indeterminate, and structurally incomplete responses), complications, quality of life, and cost-utility.

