### Objectives

#### Primary objective

To assess the non-inferiority of total thyroidectomy alone as compared to total thyroidectomy with bilateral prophylactic central compartment neck dissection in terms of the rate of complete remission (excellent response) at 1 year after randomization, for differentiated thyroid cancer cT1bT2N0. We hypothesize that the rate of complete remission after thyroidectomy alone is not inferior to the rate of complete remission after thyroidectomy with PND by more than 5% at 1 year.

The primary criterion is the rate of patients *in complete remission* (excellent response) at 1 year after randomization (8+/2 months post-^131^I) as defined by the presence of all 3 criteria:Normal whole body scan (SPECT-CT) performed after the administration of 30 mCi (1.1 GBq) of 131I administered within 2–4 months following surgery,Normal neck ultrasound 8+/−2 months after the ^131^IUnstimulated ultrasensitive thyroglobulin while on L-thyroxine treatment (usTg/LT4) ≤ 0.2 ng/mL) without anti-Tg antibodies (TgAb) 8+/−2 months after administration of ^131^I

In this network’s previous study, 94% of the low-risk patients (including 12% T2N0) were in complete remission 1 year after surgery and administration of 131I after rhTSH [40]. In a similar prospective multicentre trial, 90.2% of the low-risk patients, including patients T1–T3 N0–N1 with or without central compartment neck dissection, were in complete remission 1 year after surgery and administration of 131I after rhTSH [42]. For low-risk patients showing an excellent response after treatment, the risk of recurrence is estimated to be 2–3% [4].

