### Criteria for discontinuing or modifying allocated interventions

Secondary exclusion will be performed for patients in whom final pathology (non-frozen section analysis but defintive pathological evaluation) does not confirm the presence of a differentiated thyroid cancer.

In no other instances does this study provide for discontinuing or modifying allocated interventions.

Reasons for withdrawal from the trial (study interventions and follow-up) may include:Lost to follow-upWithdrawal of consentDeath

If a patient does not return for a scheduled visit, every effort will be made to contact them. In any case, every effort will be made to document the patient outcome and all attemps should be documented in the corresponding medical file. The investigator will inquire about the reason for withdrawal, request the patient to return for a final visit, if applicable, and follow up with the patient regarding any unresolved adverse events. The early termination final visit should include all assessments listed for the End of Study visit.

If the patient withdraws their consent for the study, no further study-specific evaluations will be performed, and no additional data will be collected. The sponsor may retain and continue to use any data and samples collected before such refusal except in case of patient opposition. Any opposition will be transmitted by the investigator to the sponsor without undue delay.

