### Determination of sample size

Non-inferiority will be demonstrated if the rate of patients in complete remission at 1 year after randomization does not differ by more than ΔL=−5%. Setting the significance level at 0.025 (one-sided) and a power of 80% requires a sample size of 598 patients without Tg antibodies (299 per group) (Nquery software).

In this network’s previous study, 94% of the low-risk patients (including 12% T2N0) were in complete biological remission at 1 year after randomization [40]. In a similar prospective multicenter trial, 90.2% of the low-risk patients, including patients T1-T3 N0-N1 with or without central compartment neck dissection, were in complete biological remission at 1 year [42].

If 5% secondary exclusion (final histopathology not differentiated thyroid cancer): 628 patients are required for randomization.

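### Remission at 3 and 5 years is compared by chi-square alone, which cannot show whether a 5-point deficit of thyroidectomy alone has been excluded

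*Protocol article*

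**What the plan says.** Under Statistical methods for primary and secondary outcomes, the 1-year endpoint gets an observed difference, a confidence interval and a comparison with -5%, which that section calls the clinically relevant difference. The same construct at 3 and 5 years gets only a test: "The rate of patients in complete remission at 3 and 5 years will be compared between groups using a chi-square test".

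The non-inferiority hypothesis is tied to year 1. Under Primary objective, remission after thyroidectomy alone "is not inferior to the rate of complete remission after thyroidectomy with PND by more than 5% at 1 year". The Secondary objectives are worded differently: "To compare total thyroidectomy and radioactive iodine" with the dissection strategy.

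Rationale: choice of comparators describes excellent response at 1 year as a surrogate endpoint. The 5-year visit is justified by reports that 77% to 81% of recurrences occur within 5 years.

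Remission at 3 and 5 years is defined under Secondary objectives and again under Oncologic secondary criteria. Both definitions describe imaging and thyroglobulin status at the visit. Neither says how a patient is classified who has already had a second operation or a second therapeutic 131I administration. Further treatment is a separate endpoint at 1, 3 and 5 years, also compared by chi-square. Among the expectations taken from retrospective series is "Difference in rate of retreatment = 8.2% at 5 years".

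**The concern.** A chi-square test asks whether the two rates differ. In a trial built to show that the lesser operation is not worse, the useful question at 3 and 5 years is how large a deficit the data still allow. A non-significant result does not answer it, because it can arise from equal rates or from a real deficit that the sample is too small to detect.

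This matters because the 3- and 5-year results are the longer-term check on a 1-year surrogate, and the article says that a positive result could lead to prophylactic dissection being abandoned in these patients. Without an interval, the later results neither support nor weaken the 1-year conclusion in a way that can be measured.

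A second, smaller point is that remission is judged at the visit. A patient re-treated successfully before year 3 or 5 counts as in remission on the definitions as written. The remission gap can then be smaller than the gap in patients who needed only their first treatment.

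**Working it through.** **Inputs.** Size, level and power come from Determination of sample size: "Setting the significance level at 0.025 (one-sided) and a power of 80% requires a sample size of 598 patients" (299 per group, margin 5 points). Allocation is 1:1. The cited remission rates, both at 1 year, are 94% and 90.2%. Assumptions: two-sided 0.05 for the secondary test, 299 evaluable per arm at 3 and 5 years, remission between 90% and 95%, and the 5-point difference carried over from year 1.

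**The plan's own figure.** n per group = 2p(1-p)(1.960 + 0.842)²/0.05².
- p = 0.95: 298.3, so 299. This matches the plan.
- p = 0.94: 354.1, so 355. p = 0.902: 555.0, so 556.

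The planning rate of 95% is back-solved; the article does not state it. No power or size is stated for 3 and 5 years.

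**Power of the chi-square for a true 5-point deficit.** Power ≈ Φ[(δ - 1.96·s0)/s1], where s0 is the pooled and s1 the unpooled standard error.
- 95% v 90%: s0 = 0.02154, s1 = 0.02144; (0.05 - 0.04222)/0.02144 = 0.363, power 64%.
- 90% v 85%: s0 = 0.02705, s1 = 0.02697; (0.05 - 0.05301)/0.02697 = -0.112, power 46%.

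Exact enumeration of both binomials (uncorrected chi-square):

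| PND v TT | Chi-square significant | Non-significant | 95% CI wrongly excludes -5 |
|---|---|---|---|
| 95% v 90% | 65.4% | 35% | 2.8% |
| 94% v 89% | 60.1% | 40% | 2.8% |
| 90.2% v 85.2% | 46.4% | 54% | 2.6% |
| 90% v 85% | 45.9% | 54% | 2.6% |

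The last two columns are different kinds of error: a missed difference, and a false claim of non-inferiority. They are shown together only because they answer the same practical question, namely how often a deficit equal to the margin would escape notice under each way of reading the data.

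**One example.** 270 of 299 (90.3%) v 255 of 299 (85.3%): difference -5.0 points, z = -1.87, p = 0.061. The 95% CI is -5.02 ± 1.96 × 2.67, or -10.2 to 0.2. The chi-square reports no significant difference; the interval shows that a deficit of twice the margin is still compatible with the data.

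**Cost of reading the interval against -5.** With no true difference, the CI excludes -5 points in 80% of trials at 95% remission, 73% at 94% and 54% at 90.2%.

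**Re-treatment.** Suppose the 8.2-point difference is an excess with TT alone (the article does not state its direction), reference remission is 94%, and a share s of the excess re-treated patients is back in remission. The remission gap is 8.2 × (1 - s).
- s = 0.5: 4.1 points, chi-square power about 45%.
- s = 0.75: 2.05 points, power about 16%.

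The separate further-treatment test, at 5% v 13.2% (5% assumed), has power Φ[(0.082 - 1.96 × 0.02352)/0.02328] = Φ(1.54) = 94%, or 95% by exact enumeration.

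**The case against.** The strongest reply is that the test fits the stated objective. Non-inferiority and the 5-point margin are set only at 1 year, the later objective is to compare, and the article lists expected differences for the secondary criteria. This stands. A reader might infer that the plan will present a non-significant 3- or 5-year result as confirmation or as no difference. No section says so, and nothing makes the primary conclusion depend on these tests. What remains is that a bare p-value leaves the useful question unanswered.

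A reader might also infer that re-treatment would hide a long-term deficit. The documents do not support that. Further treatment, with number and indication, is a pre-specified endpoint at the same visits, and its test would reveal an 8.2-point gap with about 95% power under the assumed rates. The masking affects the remission figure, not the trial's ability to see the problem. How earlier re-treatment is classified could also be settled in an analysis plan that is not shown.

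A third inference is that crude proportions are inadequate because loss, withdrawal and death are possible over 5 years, so that competing-risk methods are required. Under an assumed 15% loss (254 per arm) the power for 5% v 13.2% falls only from 95% to 91%, no bias is shown, and the article itself describes mortality as very low. That request is not made here.

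Finally, carrying the 1-year margin to later visits is a proposal and has a price, shown in the working.

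**Conclusion.** The point holds as an improvement to a stated method. For remission at 3 and 5 years the plan fixes a test of difference with no estimate or interval. At 299 per arm, a true deficit of 5 points would be non-significant in about 35% to 54% of trials, depending on whether remission with dissection is 95% or 90%. These figures rest on a two-sided 0.05 level, full retention to year 5 and rates close to those cited for year 1; loss to follow-up would make the chi-square miss such a deficit more often. The analysis does not contradict the protocol's objectives and does not affect the 1-year primary analysis. The re-treatment point is secondary and justifies a sensitivity analysis only.

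**What to change.** For remission at 3 and 5 years, report the TT minus PND difference with a two-sided 95% confidence interval, in place of the chi-square or beside it. State in advance that the 5-point difference used at 1 year is carried over as a descriptive reference, and that no formal non-inferiority claim is made at these visits.

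Add one sensitivity analysis in which a second operation or second therapeutic 131I administration before the visit counts as not in remission, and read it alongside the further-treatment endpoint.

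The change is to wording in the analysis section. It needs no extra patients, and further treatment is already to be reported at the same visits. The downside is that later results may appear as inconclusive: even with no true difference, the interval would exclude -5 points in only about 73% of trials at 94% remission and 54% at 90.2%.
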